#### Participant eligibility

2.4.2

A total of 98 subjects will be recruited from our multidisciplinary ICU if they fulfill the inclusion criteria and do not have any exclusion criteria. Figure 1 shows the overview of the recruitment process.

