#### Inclusion criteria

2.4.3

(1)Age 18 to 85 years old;(2)Met the criteria of Sepsis 3.0^[20]^, which defines sepsis as infection + sequential (sepsis) organ failure assessment score (SOFA) ≥ 2 points within the first 24 hours;(3)First ICU admission and the patient should be expected to survive within the first 48 hours;(4)Informed consent was signed by the patient or their next to kin;(5)The RF_CSA_ decreased more than 9.24%^[21]^ after ICU admission;(6)Alive during the ICU stay.

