#### Acupuncture treatment

2.5.1

According to the patient's (and/or their relatives’) willingness and the clinical routine, a group of physicians will assess the acupuncture treatment within 24 hours in patients who meets the inclusion criteria 1 to 5. All physicians are required to have at least 3 years (or 300 hours) of practical experience with acupuncture. The acupuncture treatment will be performed by stainless steel needles (0.30 mm × 40 mm; 0.30 mm × 25 mm; Suzhou Medical Supplies Factory Co., Ltd., Suzhou City, China). The acupuncture treatment will be performed by the technique of lifting, thrusting, twirling and rotating the needle until the patient is being “De-qi” (getting a numbness or other acupuncture feeling). Two points that do not cross the joint will be chosen for electrical stimulation. The needle will be kept in place for approximately 30 minutes. By the time we remove the needles, a clean cotton balls will be pressed to the skin to prevent bleeding.

All patients must be treated at “3 obligatory basic acupuncture points”: ST36, ST40 and LI10. Furthermore, at least 3 additional acupuncture points will be selected according to the principles of traditional Chinese medicine (for example, if the patient has a mental disorder manifestation, acupoints such as GV20, GV24, and EX-HN3 can be added to promote the patient's waking). Additional acupoints could be applied, and ear acupuncture points might also be included. All acupoints selected in each session will be recorded. A traditional Chinese syndrome diagnosis is required, and the diagnosis will be documented. Acupuncture treatment will be performed twice a day and lasts for 30 minutes. If the included subjects do not meet the exclusion criteria and do not terminate their participation in study, they will receive acupuncture treatment during their entire ICU stay. If the patient is discharged from the ICU, the acupuncturist will continue to follow the patient until the 14-day acupuncture session is completed. Both the acupuncture group and the control group will receive basic sepsis treatment. The selection of acupuncture points is listed in Table 1.

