### Study groups

2.7

Since this study is a real-world study, the grouping of the study subjects was determined by the actual observations. Therefore, no randomization of groups was set in this study. The subjects will be as allocated into 2 arms.

Group 1: acupuncture group

When the participant meets the inclusion criteria (1 to 5), the acupuncturist will assess the conditions for patient treatment. Patients can enter this group and have acupuncture treatment if they do not have specific conditions (such as edema, coagulopathy, acupoints local skin and soft tissue infection, and rejection of acupuncture treatment) that are not suitable for acupuncture.

Group 2: control group

Patients who are not suitable for acupuncture or are not willing to receive acupuncture could enter this group. In addition to basic treatment, patients in this group will be prescribed exercises, such as early in-bed activities or wheelchair activities.

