### Outcome

2.8

The primary outcomes will be the decline of RF_CSA,_ the MRC-SS and time-to-event (defined as all-cause mortality or unplanned readmission to the ICU due to invasive ventilation). The activities of daily living will be accessed by the motor item of the Functional Independence Measure (FIM^TM^). Secondary outcome includes the expression level of MSTN, ICU length of stay, length of hospital stay, duration of invasive/non-invasive mechanical ventilation. The outcomes will be measure as follow:

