#### Collecting healthcare data within the ICU stay

2.8.6

During the screening period, the relevant subject information will be completed, and baseline demographic-related items will be collected. The SOFA score, the immediate acute physiology and chronic health evaluation II score (and SAPS score), the GCS score, body temperature, mechanical ventilation or not, the infection site, the pathogenic examination before the administration of antibiotics or use of vasoactive drugs, arterial blood gas analysis, blood routine, coagulation function, liver function, kidney function, heart function, infection index, urine pregnancy test (female subjects), and an electrocardiogram will be recorded during this period. The length of the first antibiotic use and whether the pathogen is sensitive to the antibiotic will be recorded after initiation.

For patients who survive and are discharged from the ICU - meeting all inclusion criteria (1 to 6) - the mechanical ventilation duration time, LOS, total hospital stay, sum sedative analgesic dose, statin dose, blood glucose level, insulin dosage, glucocorticoid dosage, protective constraints, and the duration of neuromuscular blockers will be additionally recorded.

Table 2 shows a general view of the data collecting and the time of acquisition for each item. We will manage all study data anonymously, and all CRFs will be labelled with a study number allocated to each individual participant. The CRF will be in both paper and electronic formats. The paper version of the CRF will be used for backup storage of data and for verification when needed. The daily management of data will be completed on the EDC system. And the details of bedside data collection are shown in Table 3.

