### Statistical analysis

2.10

All available data will be analyzed descriptively. For continuous data, the normality test will be applied at the very beginning of the analysis. We will bewrite the results as the means, standard deviations, and 95% confidence intervals (CIs) for continuous data that conform to the normal distribution; medians, quartiles, and ranges for rank data and continuous data that do not fit the normal distribution; and percentages for discrete data.

The change in the RF_CSA_ from baseline will be analyzed by a generalized additive mixed model of repeated measures design. Analysis of the time-to-event outcome (at day 28, day 90, six months, and 1 year after the admission of ICU) will be conducted by applying Kaplan-Meier curves. Kaplan-Meier survival curves will be performed to describe the survival rate between the 2 groups, and the log-rank method will be used to compare the survival rates of the acupuncture group and control group. Multivariate Cox proportional hazard regression models will be used to analyze several constituents (such as acute physiology and chronic health evaluation-II, SOFA score, demographic and diagnostic data), adjust for covariates, and correct for confounding. Our team will use similar approach mentioned above to analyze secondary outcome measures when they can be expressed as time-to-event outcome dimensions. All regression analyses (generalized additive mixed models, log-rank analysis, multivariate Cox proportional hazard regression models) will include the same covariates as the primary analysis. If there are any measurable differences between the 2 study groups with regard to prognostic factors, a propensity score analysis will be applied to assess the sensitivity of the results to any treatment allocation biases. The propensity score will be set for the main outcome. After the 2 sets of data are analyzed according to the previous analysis, the patients will be matched with the propensity score, and then the main outcomes of the matched 2 groups will be compared again to see if there are any similarities or differences between the 2 groups before and after the match. If they are the same, the results are stable; however, a difference means that there are factors affecting the evaluation of the outcome before the match, and these factors will need to be explained.

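### Taken literally, inclusion criterion (6) drops ICU deaths after group entry and treatment start, which hides any effect on ICU mortality from a primary outcome that counts all-cause death

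*Protocol article*

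**What the plan says.** All references are to the protocol article.

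- **2.4.2 Participant eligibility:** "A total of 98 subjects will be recruited from our multidisciplinary ICU if they fulfill the inclusion criteria".
- **2.4.3 Inclusion criteria:** the sixth criterion is "Alive during the ICU stay".
- **2.5.1 Acupuncture treatment:** "a group of physicians will assess the acupuncture treatment within 24 hours in patients who meets the inclusion criteria 1 to 5". After that, "they will receive acupuncture treatment during their entire ICU stay".
- **2.7 Study groups:** "When the participant meets the inclusion criteria (1 to 5), the acupuncturist will assess the conditions for patient treatment". Allocation is not randomised.
- **2.8 Outcome:** one primary outcome is "time-to-event (defined as all-cause mortality or unplanned readmission to the ICU due to invasive ventilation".
- **2.8.6 Collecting healthcare data within the ICU stay:** a second list of items opens with "For patients who survive and are discharged from the ICU - meeting all inclusion criteria (1 to 6". It includes ventilation time, length of stay, sedation, glucocorticoid dose and neuromuscular-blocker duration.
- **2.10 Statistical analysis:** the event outcome is analysed "at day 28, day 90, six months, and 1 year after the admission of ICU".

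Two sections point the other way. The closing paragraph of 2.4.4 restates eligibility as sepsis, muscle loss beyond the threshold and consent, without criterion (6). Section 2.8.7 follows patients to the end of follow-up or to death.

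**The concern.** Criteria 1 to 5 can be judged when a patient enters a group. Criterion (6) can be judged only when the ICU stay ends, after acupuncture has begun. If it is a condition of inclusion, survival under treatment decides who is in the trial.

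This matters in three ways.

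- The primary time-to-event outcome is meant to count deaths from ICU admission, but an included patient cannot have died in the ICU. The ICU stay becomes immortal time.
- If acupuncture changes ICU survival, the two groups of survivors differ in case mix because of the treatment. Baseline adjustment cannot undo that. The muscle-area and muscle-strength comparisons inherit the same selection.
- Length of stay and ventilation time are secondary outcomes, but 2.8.6 places them in the list for patients who survive and are discharged.

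**Working it through.** **1. Order of events**

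| Step | Section | Criteria needed |
|---|---|---|
| Assessment for acupuncture | 2.5.1 | 1 to 5 |
| Group entry | 2.7 | 1 to 5 |
| Treatment through the ICU stay | 2.5.1 | none further |
| Survived and discharged from the ICU | 2.8.6 | 1 to 6 |

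The split between 1 to 5 and 1 to 6 is used consistently in three sections. Criterion (6) therefore does not mean alive at enrolment; expected early survival is already covered by criterion (3).

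**2. The plan's own figure**

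The only stated calculation is 39 per arm, raised to 49 (section 2.3). With two-sided alpha 0.05 (sidedness is not stated) and the unpooled formula, n = (1.960 + 0.842)² × (0.125 × 0.875 + 0.393 × 0.607) / 0.268² = 38.02, so 39. With 20% dropout, 39 / 0.8 = 48.75, so 49. The figure reproduces. It rests on polyneuromyopathy incidence, so removing criterion (6) does not change it.

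**3. How many deaths are involved**

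The article gives no ICU mortality, so 10/20/30/40% is assumed. If 98 patients enter on criteria 1 to 5, 98 × (1 − d) leaves about 88/78/69/59. If 98 ICU survivors are required, 98 / (1 − d) means that about 109/123/140/164 must enter, and 11/25/42/66 ICU deaths fall outside the trial.

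**4. Masking, without frailty**

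Let d be the ICU death risk and q = 20% (assumed) the later one-year event risk, equal in both groups. The full-cohort risk is d + (1 − d)q; the survivors-only risk is q.

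- Share of control events removed, d / [d + (1 − d)q]: 0.20/0.36 = 56%, 0.30/0.44 = 68%, 0.40/0.52 = 77%.
- Benefit, d = 15% vs 30%: full cohort 0.32 − 0.44 = −12 points; survivors 0.
- Harm, d = 45% vs 30%: full cohort 0.56 − 0.44 = +12 points; survivors 0.

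**5. Possible reversal, with frailty**

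*Two strata.* Half the patients are frail. ICU death in the frail is 30% with acupuncture and 50% in controls; in the rest it is 10%. Later event risk is 50% in the frail and 10% in the rest.

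- Controls: survivors 0.25 + 0.45 = 0.70; later events 0.125 + 0.045 = 0.17. Full 0.30 + 0.17 = 0.47; survivors-only 0.17/0.70 = 0.243.
- Acupuncture: survivors 0.35 + 0.45 = 0.80; later events 0.175 + 0.045 = 0.22. Full 0.20 + 0.22 = 0.42; survivors-only 0.22/0.80 = 0.275.
- Difference: −5.0 points in full, +3.2 points among survivors.

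*Continuous frailty.* Z is standard normal. ICU death: logit p = a + 1.2Z + log(OR) in the acupuncture group. Later events: hazard 0.35 × 2.0^Z per year, with no treatment effect after the ICU. Integrating over Z gives one-year risks in %, control then acupuncture (differences from unrounded values):

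| OR for ICU death | Control ICU mortality | Full cohort | Diff. | Survivors only | Diff. |
|---|---|---|---|---|---|
| 0.5 | 20% | 43.4, 39.0 | −4.4 | 29.2, 30.5 | +1.3 |
| 0.5 | 30% | 49.4, 43.2 | −6.2 | 27.7, 29.3 | +1.5 |
| 2 | 20% | 43.4, 49.7 | +6.3 | 29.2, 27.7 | −1.5 |
| 2 | 30% | 49.4, 57.4 | +8.0 | 27.7, 26.0 | −1.7 |

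**6. Sensitivity of the sign** (survivors' control one-year risk set to 30%; ICU mortality 20% and 30%)

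- OR 0.5 and post-ICU hazard ratio 0.9: survivors-only about 1 point lower; full cohort 6.4 and 7.9 points lower. Sign correct, most of the effect lost.
- OR 2 and post-ICU hazard ratio 1.1: survivors-only 0.6 and 0.3 points higher; full cohort about 8 and 9 points higher. Sign correct, nearly all lost.
- Weaker frailty (0.6 per SD, hazard ratio 1.4 per SD), no post-ICU effect: survivors-only differences of about 0.4 to 0.7 points, still of the wrong sign.

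**The case against.** **No section says that ICU deaths are dropped.** This stands. The removal follows from listing (6) as an inclusion criterion. The restatement in 2.4.4 omits it, 2.8.7 follows patients until death, and 2.8.6 could be read as only an extra data tier for survivors. The flowchart and timeline are not shown. But neither 2.4.4 nor 2.8.7 says that ICU deaths are kept, and 2.4.2 ties the 98 subjects to the inclusion criteria. At best the sections conflict.

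**A reader might infer that the estimated effect always has the wrong sign.** The documents do not support that. Reversal needs frailty and little or no effect after the ICU, and every rate used is assumed. A reversed difference of 1 to 2 points could not be detected with 49 per arm in any case.

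**A reader might infer that the safety objective fails.** It does not. Sections 2.12 and 2.13 require adverse event and serious adverse event reporting and regular safety summaries to the data monitoring committee, and neither is limited by criterion (6). What is lost is the between-group mortality estimate.

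**It is a pilot, and an analysis plan may settle it.** The second research objective (1.1) covers long-term prognosis and safety, and the planned multicentre study could inherit the rule. Criterion (6) is a stated eligibility rule, not an omitted detail. An analysis plan could not recover data that were never collected on patients who died.

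**Conclusion.** The point holds as a stated rule that biases a primary outcome, together with a conflict between sections. Read literally, criterion (6) conditions the comparison on survival after treatment starts.

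The firm result is masking: an effect confined to ICU mortality appears as zero among survivors, or as a small difference produced by selection alone. This does not depend on the chosen rates. The size does. With control ICU mortality of 20-30%, strong frailty, odds halved or doubled and no later effect, a true difference of about 4 to 8 points becomes 1 to 2 points of the opposite sign. The opposite sign is one scenario, not a general result. Deaths after ICU discharge are still counted, and safety surveillance is intact.

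**What to change.** 1. Delete criterion (6) as a condition of inclusion, and bring 2.4.2, 2.4.3, 2.4.4 and 2.8.6 into line.
2. Fix the cohort when criteria 1 to 5 are met and the group is recorded.
3. After that point, do not use exclusion (10), ICU stay under 7 days, or exclusion (12), therapy withdrawal, to remove patients from the analysis. Both can be decided after treatment starts, and (10) alone would still remove deaths before day 7. Consent refused before entry remains an exclusion.
4. Start the time-to-event clock at cohort entry. Criterion (5) requires muscle loss after admission, so entry is later than admission; if the clock stays at ICU admission, use left truncation.
5. Count every death from entry, including ICU deaths.
6. Collect the second data list of 2.8.6 for all entered patients.
7. Report ICU survivors only as a labelled subset.

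The cost is a protocol amendment and some added case report form work for patients who die in the ICU. No new procedure is needed. Observed event rates will be higher than in a survivors-only cohort.

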#### Exclusion criteria^[1,2]^

2.4.4

(1)A confirmed pregnancy or the urine β-HCG test is positive;(2)The questionnaires (MRC-SS and FIM^TM^) or consent form could not be completed due to cognitive abnormalities.(3)A newly diagnosed primary neuromuscular disease when admitted to the hospital;(4)Leg amputation, pelvic/femoral fractures or knee/hip replacement that prevent the measurement of the RF_CSA_;(5)Malnutrition (BMI less than 18.5 kg/m^2^) or cachexia;(6)Metastatic tumors (PD) or ongoing chemotherapy;(7)Cardiorespiratory arrest or imminent death;(8)Long-term corticoid treatment;(9)Could not walk independently before sepsis onset;(10)ICU length of stay (LOS) < 7 days^[2]^;(11)Sepsis onset more than 5 days before ICU admission^[2]^;(12)Therapy withdrawal or consent refusal.

Patients are eligible if they are diagnosed with sepsis, their RF_CSA_ decreased more than 9.24%^[21]^ from baseline, and informed consent has already acquired from the patient and/or immediate family member. A case report form (CRF) will be completed, and the RF_CSA_, MRC-SS score and other relevant data will be obtained, for all eligible and consenting patients. We will use the RF_CSA_ to assess the changes in muscle morphometry; the MRC-SS will be used to assess whether patients meet the diagnostic criteria of ICU-acquired weakness and to observe mortality, rehospitalization, reintubation and mechanical ventilation and other relevant indicators during the 1-year follow-up.

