#### Electronic data capture (EDC) System

2.4.1

The Department of Critical Care Medicine at the First Affiliated Hospital of Guangzhou University of Traditional Chinese Medicine has already deployed a cloud-based EDC system (website: https://study.empoweredc.com/site/203). Each patient will be assessed within 24 hours after ICU admission, and patients who meet the sepsis diagnosis will be entered into the system. Peripheral serum will be collected prospectively at baseline and at subsequent time points and will be stored in the biological sample bank (Ling-Nan Medical Research Center) to test MSTN expression levels. Patients who meet the SIM diagnosis will be marked in the EDC according to the diagnostic criteria. Two intensivists will measure the RF_CSA_ of the sepsis patients at the measurement time point and will then enter the data into the EDC system; a consistency evaluation will be performed. One ICU specialist and 1 neurologist will evaluate the medical research council sum-score (MRC-SS) of the SIM patients.

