#### Assessment of MRC-SS

2.8.2

Peripheral muscle strength will be measured according to the Medical Research Council sum-score (MRC-SS), which will result in a range of 0 to 60. Higher scores indicate greater muscle strength. Three muscle groups of each extremity will be tested bilaterally: shoulder abductors, elbow flexors, wrist flexors, hip flexors, knee extensors, and ankle dorsiflexors. Muscle weakness will be defined as an MRC-SS less than 48.^[25–27]^ When the patient is in a condition in which the MRC-SS cannot be fully evaluated (eg, 1 or more limb amputations or fractures; the limb cannot move due to indwelling tubing), a mean MRC-SS of less than 4 is used to indicate muscle weakness.^[26]^

Muscle strength will be evaluated at the first awakening and at ICU discharge. The first awakening is defined as the first day when the participant is alert, has a Richmond sedation and agitation scale between -1 and 1 (the Richmond sedation and agitation scale score range from -5 to +4, and -1 to +1 is the ideal score range for full cooperation to the MRC-SS test), and is able to follow at least 3 of the De Jonghe 5-command criteria.^[27]^

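### The neuromuscular exclusion covers only newly diagnosed disease, so known disease in patients who still walk can enter and lower an absolute primary MRC-SS

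*Protocol article*

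**What the plan says.** All references are to the protocol article.

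- **Exclusion criteria (2.4.4), item 3:** "A newly diagnosed primary neuromuscular disease when admitted to the hospital". Item 9: "Could not walk independently before sepsis onset".
- **Inclusion criteria (2.4.3), item 5:** the muscle criterion is that the RF_CSA "decreased more than 9.24" per cent after ICU admission. There is no strength criterion for entry.
- **Outcome (2.8):** the primary outcomes are the decline of RF_CSA, "the MRC-SS and time-to-event (defined as all-cause mortality or unplanned readmission to the ICU due to invasive ventilation").
- **Closing paragraph of 2.4.4:** "the MRC-SS will be used to assess whether patients meet the diagnostic criteria of ICU-acquired weakness".
- **Assessment of MRC-SS (2.8.2):** "Muscle strength will be evaluated at the first awakening and at ICU discharge", and "Muscle weakness will be defined as an MRC-SS less than 48".
- **Electronic data capture (2.4.1):** "One ICU specialist and 1 neurologist will evaluate the medical research council sum-score (MRC-SS) of the SIM patients".
- **Study groups (2.7):** allocation follows suitability for acupuncture and the patient's willingness; there is no randomisation.

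**The concern.** An exclusion for primary neuromuscular disease serves to keep weakness of another origin out of a cohort studied for weakness arising in sepsis. Disease known for years is as much a competing cause as disease found at admission. The words that limit item 3 to new diagnoses leave the known cases in.

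Three things are at stake. First, one primary outcome would include deficits that predate sepsis. Second, the below-48 classification would attribute some of that weakness to the ICU stay. Third, the first research objective asks whether the RF_CSA decline underlies the weakness seen in septic patients, and weakness with an older cause blurs that relation. The study is also meant as the pilot for a multicentre study, so the wording could be carried forward.

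**Working it through.** This is a question of eligibility wording, and the plan states no figure for it. The only related calculation is the sample size, which does not depend on item 3. From 12.5% and 39.3%, two-sided α = 0.05 (sidedness assumed), power 0.80 and unpooled variance:

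n = (1.960 + 0.842)² × (0.125 × 0.875 + 0.393 × 0.607) / 0.268² = 38.02, rounded up to 39 per group.

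This matches the stated 39, and rewording item 3 leaves it unchanged.

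**Step 1. Does any other criterion close the gap?** Take a patient with a neuromuscular disease known before admission who walked independently, and go through the six inclusion and twelve exclusion criteria.
- Item 3 does not apply, because the disease is not newly diagnosed.
- Item 9 does not apply, because the patient could walk.
- Items 5 (malnutrition or cachexia) and 8 (long-term corticoid treatment) might remove such a patient, but only incidentally.
- The remaining exclusions do not concern neuromuscular history.
- Inclusion item 5 needs an RF_CSA fall after ICU admission, which this patient can show like any other septic patient.

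The patient is eligible under the text as written.

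**Step 2. Which primary outcomes are exposed?**
- *RF_CSA* is analysed as change from baseline (Statistical analysis, 2.10). A stable earlier loss of muscle is already in the first value and largely drops out.
- *Death or unplanned ICU readmission* is not scored from strength.
- *MRC-SS* has no pre-sepsis value. Its cut-off is absolute, and 2.10 does not say that it will be analysed as a change. This outcome is directly exposed.

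**Step 3. How does a prior deficit act on the cut-off?** Section 2.8.2 tests six muscle groups on both sides, 12 in all, with a total of 0 to 60, so each scores up to 60 / 12 = 5. The alternative rule of a mean below 4 agrees with the cut-off, since 12 × 4 = 48.

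Let d be the chronic deficit and a the further loss during the illness, both in whole points. Weakness is recorded when 60 − d − a < 48, that is, when a ≥ 13 − d. The documents give no value of d, so these are illustrations:

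| Chronic deficit d (assumed) | Further loss needed to be recorded as weak |
|---|---|
| 0 | 13 |
| 4 | 9 |
| 8 | 5 |
| 12 | 1 |
| 13 or more | 0 |

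The larger the earlier deficit, the less acute loss is needed for the patient to be classed as having ICU-acquired weakness.

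**Step 4. Can the effect on the group comparison be sized?** That needs the number of such patients, their deficits and their split between groups. The protocol gives none of these, nor an SD or target difference for MRC-SS. No figure is offered.

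**The case against.** **The SIM label.** A reader might infer that long-standing weakness is scored as sepsis-induced myopathy. The documents do not support this. Muscle entry rests on an acute within-patient fall in RF_CSA, while an MRC-SS below 48 is the document's marker of weakness and is used for ICU-acquired weakness. A patient with stable chronic weakness and no acute muscle loss is not enrolled. Every affected patient would have acute wasting on top of the old deficit. What remains is contamination of the absolute score and of the below-48 classification.

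**A sizeable bias.** A reader might also assume a deficit and an excess of such patients in one group, and derive a shift in the mean difference. Both inputs would be invented. An imbalance large enough to matter also fits poorly with the expectation that few such patients exist.

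**Two measurements.** A fixed deficit would cancel in a change from first awakening to ICU discharge. This is correct, but the protocol does not state that analysis. Suitability for acupuncture is assessed within 24 hours in patients meeting inclusion criteria 1 to 5 (2.5.1), so treatment may already have begun by first awakening.

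**Adjustment.** Section 2.10 plans covariates from an open list that includes diagnostic data, and a propensity-score analysis if prognostic factors differ. This could cover a known neuromuscular diagnosis, although none is named. It would ease imbalance between groups, but would not correct the classification of an individual patient.

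**Conclusion.** The point holds in a limited form. As written, item 3 admits a patient with known neuromuscular disease who walks independently and meets the RF_CSA criterion, and no other criterion reliably removes that patient. The chronic deficit lowers a primary outcome scored in absolute terms and can be counted as ICU-acquired weakness. With non-randomised groups it may be unbalanced.

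The exposure is confined to one of the three primary outcomes and does not reach the SIM entry criterion. The number of patients is unknown and probably small; that is a judgement, not a figure from the documents. The conclusion rests on reading item 3 literally and on MRC-SS being used as an absolute score, which is how the protocol describes its cut-off. It is a wording defect worth correcting because the correction is simple, not because a large bias has been shown.

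**What to change.** Reword exclusion (3) to: *any primary neuromuscular disease, known before or newly diagnosed at this admission*. Leave exclusion (9) as it stands.

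Do not extend the item to every other documented limb weakness. In a pragmatic study of adults up to 85 years, that could remove walking patients with an old stroke or neuropathy, which is a separate trade-off.

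The cost is one phrase and the loss of a few otherwise eligible patients. The screening items in 2.8.6 do not name a neuromuscular history, so it should be asked for explicitly. Exclusion (9) already requires asking about function before sepsis, so the added work is slight. The sample size is unaffected.

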#### Measurement of RF_CSA_

2.8.1

We will measure the RF_CSA_ on days 1, 3, 5, 7, 10, and 14 by B mode ultrasonography, using a 12L-SC (8.0-13.0 MHz, 7cm) linear array (Venue 50, GE Healthcare) at the First Affiliated Hospital of Guangzhou University of Chinese Medicine. RF_CSA_ will be measured on days 18, 21, 24, 28 if the patient continues to stay in the ICU. Patients will be prone to a 30° upwards incline at the head, except where the clinical conditions dictate otherwise. An excess of gel will be applied to minimize distortion. The transducer should be placed perpendicularly along the superior aspect of the upper leg, two-thirds of the distance between the anterior superior iliac crest and the superior patellar border. RF_CSA_ will be taken as an average of 3 consecutive measurements within 10% of 1 another. (A larger RF_CSA_ indicates a larger muscle mass). The point of measurement will be marked on the skin, and the same limb and location will be measured at each time point.^[1,24]^

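### Exclusion (10), ICU stay under 7 days, can take effect after group entry and treatment start, so it selects on a secondary outcome; inclusion (6) does the same with ICU survival

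*Protocol article*

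**What the plan says.** All references are to the protocol article.

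- **Exclusion (10), section 2.4.4:** "ICU length of stay (LOS) < 7 days". It is worded as an actual stay, not an expected one, and no time of application is given.
- **Inclusion (5), section 2.4.3:** the rectus femoris cross-sectional area must have "decreased more than 9.24" per cent since ICU admission.
- **Scan days, section 2.8.1:** the area is measured "on days 1, 3, 5, 7, 10, and 14 by B mode ultrasonography".
- **Treatment decision, section 2.5.1:** "a group of physicians will assess the acupuncture treatment within 24 hours in patients who meets the inclusion criteria 1 to 5". Section 2.7 assigns the acupuncture group on the same trigger. Neither inclusion (6) nor a completed 7-day stay is needed first.
- **Continuing eligibility, section 2.5.1:** treatment goes on "If the included subjects do not meet the exclusion criteria and do not terminate their participation in study", so the exclusion criteria still apply to patients already included.
- **After ICU discharge:** section 2.5.1 says "If the patient is discharged from the ICU, the acupuncturist will continue to follow the patient until the 14-day acupuncture session is completed". Section 2.8.7 says the researcher carries out no intervention of any kind after ICU discharge.
- **Outcomes, section 2.8:** "Secondary outcome includes the expression level of MSTN, ICU length of stay, length of hospital stay". One primary outcome is time-to-event, "defined as all-cause mortality or unplanned readmission to the ICU due to invasive ventilation".
- **Inclusion (6), section 2.4.3:** the patient must be alive during the ICU stay. Section 2.8.6 records length of stay and related items for ICU survivors who meet inclusion 1 to 6.

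**The concern.** An eligibility rule should rest on facts known when the patient enters the comparison. Exclusion (10) does not do so for a patient who qualifies at day 3 or day 5, joins a group and leaves the ICU alive on day 5 or 6. Read literally, that patient becomes ineligible because of what happened after entry.

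Two things are at stake. First, ICU length of stay is an outcome, and the rule cuts it off below 7 days in both groups. If acupuncture shortens the stay, more acupuncture patients are removed, and they are the ones who did well. Second, the muscle, strength and event outcomes are then compared in groups that may have been selected differently. Section 2.10 plans a propensity score analysis for allocation bias. That can balance measured prognostic factors among patients who are kept, but it cannot restore patients removed after entry.

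Inclusion (6) has the same fault for survival: it removes patients who enter a group and then die in the ICU, although all-cause mortality is part of a primary outcome.

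**Working it through.** **Timing.** The scans fall on days 1, 3, 5, 7, 10 and 14 (section 2.8.1). A fall from baseline can first be seen at day 3. Assessment for acupuncture follows within 24 hours (section 2.5.1).

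| Inclusion (5) first met | Group entry about | Is a stay of 7 days already known? |
|---|---|---|
| Day 3 | Day 3–4 | No |
| Day 5 | Day 5–6 | No |
| Day 7 or later | Day 7 or later | Essentially yes |

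Exclusion (10) therefore acts after entry only in the first two rows.

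**Size.** The plan has no length-of-stay figure to reproduce, and its sample size does not depend on one. The following is an illustration.

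Assumptions: log-normal ICU stay *T*; control median *m* = 10 days; log-SD *s* = 0.6; entry at day 4; acupuncture shortens the stay by 20%.

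Formulas, for a cut at *a* days:
- z = (ln a − ln m)/s and P(T < a) = Φ(z).
- Geometric mean given T ≥ a: m·exp(s·λ), with λ = φ(z)/(1 − Φ(z)).

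*Model A: acupuncture multiplies the whole stay by 0.8 (median 8 days).*

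| | Control | Acupuncture | Ratio |
|---|---|---|---|
| P(T < 4) | 0.063 | 0.124 | |
| P(T < 7) | 0.276 | 0.412 | |
| Geometric mean, T ≥ 4 | 10·exp(0.6 × 0.133) = 10.83 | 8·exp(0.6 × 0.234) = 9.20 | 0.85 |
| Geometric mean, T ≥ 7 | 10·exp(0.6 × 0.462) = 13.19 | 8·exp(0.6 × 0.662) = 11.90 | 0.90 |

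Excluded by (10) among patients still in the ICU at day 4:
- control: (0.276 − 0.063)/(1 − 0.063) = 22.7%
- acupuncture: (0.412 − 0.124)/(1 − 0.124) = 32.9%

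The share of the log effect lost to the rule is 1 − ln(0.902)/ln(0.850) = 0.37, a little over a third.

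*Model B: acupuncture shortens only the stay after day 4, T′ = 4 + 0.8(T − 4).*
- T′ < 7 when T < 4 + 3/0.8 = 7.75, and P(T < 7.75) = Φ(−0.425) = 0.335.
- Acupuncture patients excluded: (0.335 − 0.063)/(1 − 0.063) = 29%. Controls stay at 23%.
- Geometric-mean ratio: 9.56/10.83 = 0.88 before the rule, 11.98/13.19 = 0.91 after it.
- Mean difference: 1.71 days before, 1.61 after, which is 6% smaller.

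**Sensitivity.**
- With the effect on the post-entry stay only, entry at day 3–4, residual median 5–10 days and log-SD 0.5–1.0, the rule drops 1–41% of controls and 3–50% of acupuncture patients. The mean difference falls by about 4–37%.
- With entry at day 6, the largest change in the same grid is from 1.65 to 1.54 days (0.11/1.65, about 7%).
- Shape matters on the absolute scale. With the effect on the whole stay and mean 10 days, an exponential stay leaves the mean difference at 2.00 days, and a gamma stay with shape 0.8 raises it from 2.00 to 2.17. On the ratio scale, the result moved towards 1 in every scenario tried.

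**The case against.** The strongest defence is that a 7-day minimum, supported by a citation in section 2.4.4, defines a prolonged-stay sepsis population. That would stand if group and time zero were both set at day 7 and the question were stated for patients still in the ICU then. The protocol instead sets group and treatment when inclusion 1 to 5 are met, and nothing limits (10) to stays that end before entry.

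It can also be said that the harm is limited: only early qualifiers are touched, the quantified outcome is secondary, and this is a non-randomised pilot. That stands, and it bounds the point.

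A reader might infer four stronger things that the documents do not support:

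- **That half the length-of-stay effect is lost.** This compares the kept ratio of 0.90 with 0.80, the ratio from admission. Being in the ICU at day 4 already gives 0.85 before (10) acts.
- **That (10) is why early deaths disappear.** Inclusion (6) removes ICU deaths at any time. What (10) adds is the loss of patients discharged alive before day 7.
- **That the effect on stay must shrink.** This needs a true benefit, and on the absolute scale it also depends on the shape of the distribution.
- **That a short stay is no obstacle to the full course.** Section 2.5.1 points that way, but section 2.8.7 contradicts it.

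**Conclusion.** The point holds in this form. For patients who meet inclusion (5) at the day-3 or day-5 scan, exclusion (10) is a condition on a secondary outcome that becomes known only after they may have entered a group and started treatment. Inclusion (6) is a condition on survival with the same defect, and it bears on a primary outcome. Both follow from the text alone. Patients who first meet inclusion (5) at day 7 or later are essentially unaffected by (10).

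The size rests wholly on assumed stay distributions and an assumed 20% benefit. In the base illustration the two groups lose visibly different fractions, and the ratio moves towards 1 by 0.03 to 0.05. The change in mean difference ranges from none, or a slight rise, to a substantial fall. Possible bias in the muscle, strength and event outcomes follows from the same selection, but it has not been quantified and its direction is not established.

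**What to change.** 1. Define the analysed cohort and time zero as the point at which inclusion 1 to 5 are met and the group is recorded.
2. Apply exclusion (10) only to ICU stays that ended before that point. Do not use (10) or inclusion (6) to remove anyone from the analysis afterwards.
3. Analyse ICU stay with death as a competing event, since ICU deaths will now be in the cohort.
4. Reconcile sections 2.4.3, 2.4.4, 2.5.1, 2.8.6 and 2.8.7 accordingly: when the exclusion criteria apply, for whom length of stay is recorded, and whether the course continues after ICU discharge. That last matter is for the investigators to settle; the two sections need only agree.

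The cost is a short amendment across these sections and collection of the section 2.8.6 items for every patient in the cohort. The planned sample size does not change. The downside is that short-stay patients contribute fewer in-ICU measurements.
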